| Number of Participants with Rationale: | 20 to 30 patients with low back pain (min. 10 per arm) and 20 healthy controls for the normative data. Based on previous studies with similar endpoints, the selected amount of participants has shown to suffice for an explorative approach with a desired power of 80% and an alpha of 0.05. |
| Study Duration:                        | September 2014 to December 2015                                                                                                                                                                                                                                                                 |
| Study Schedule:                        | Begin recruiting: January 2015
Last assessment: December 2015                                                                                                                                                                                                                                |
| Investigator and project leader:       | [name]
[contact]
[contact]                                                                                                                                                                                   |
| Study Centre:                          | Reha Rheinfelden
[name]

[name]                                                                                                                                                                                                                                   |
| Statistical Considerations:            | Student T-Test will be applied for group comparison at Baseline for cross-sectional comparison of LBP group with healthy group.

Repeated measure ANOVA with post-hoc analysis will be applied to test therapy effects.

Effect size will be calculated with Guyatt's effect size.  |
| GCP Statement:                         | This study will be conducted in compliance with the protocol, the current version of the Declaration of Helsinki, the ICH-GCP or ISO EN 14155 (as far as applicable) as well as all national legal and regulatory requirements.                                                                 |

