## 6. STUDY DESIGN

### 6.1 General study design and justification of design

The intended procedures and study stages are summarised in Table 1 and Figure 1. Patients will be recruited from the out-patient department of the study site (Reha Rheinfelden) and public advertisement. In a cross-sectional study, baseline (BL) values are recorded to assess and to identify expected discrepancies in postural behaviour in a group-wise comparison (healthy vs. patients with LBP). In a pilot randomised sham-controlled trial (RCT) with parallel groups and blinded assessors, the effects of added SMT to conventional therapy in comparison to added LIT will be evaluated on three additional measurement events. The primary endpoints are pain and function before ( $T_0$ ) and after 9 treatments during 5 weeks (twice a week). Short-term effects will be evaluated within a week after the last training session ( $T_1$ ). Long-term effects will be tested four weeks after the last training session ( $T_2$ ).

*Screening and pre-intervention assessments:* Potential participants will be informed (personal or by phone and email) of the study procedures, risks and expenses, and possible benefits (according to the patient information sheet approved by the competent ethical committee, CEC). After written and oral information, the patient will have one to three days to consider participation before giving informed consent. Once written consent is provided, a baseline measurement will take place 2 to 4 days prior to therapy commencement. For healthy participants there is no time constraint. An internal rheumatologist will confirm the diagnosis for patients who are not referred to the clinic by their treating physicians. The BL assessment will reveal whether all eligibility criteria are fulfilled and whether trial participation is granted. Patients will also be asked to give a second oral consent to further participate in the trial. Once included and randomised for treatment groups, all analysis will follow intention-to-treat principles (as-per-case analysis will also be conducted).  $T_0$  will be conducted immediately before first treatment to ensure a stable baseline (4 to 7 days after BL).

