## 9.2 Assessments of outcomes

### 9.2.1 Assessment of primary outcome

Whilst preparing the setup and software configuration, the subject will be given 10 minutes time to fill in the personal data sheet, including the VAS scales for pain, and the ODI questionnaire for functional status. The questionnaires will be filled in by the patients at every measurement event (BL, T0, T1, and T2).

Self-reported impairment in daily activities will be assessed using the German version of the Oswestry Disability Index (ODI-D), which shows a good reliability. The ODI has ten sections about daily activities (pain, body hygiene, lifting objects, walking, sitting, standing, sleeping, sexual behaviour, social life, and travelling). Each section can be rated from 0 (no pain during activity or pain getting worse) to 5 (I cannot do it myself). The total score is in percentage of the total 50 points, if each section was answered (45, if 9 sections were answered, and so on). The end score will be from 0% (minimal impairment) to 100% (bedridden). A change of 4 points is considered as clinically relevant [26].

Self-reported pain will be assessed using the German version of the Visual Analogue Scale (VAS). It shows a good reliability with a correlation of 0.937 between the first and the second assessment. The VAS is a 100mm line with two endpoints representing the extreme states "no pain" and "pain as bad as it could be". A minimum of 13 mm difference on the scale is considered as clinical relevant [26].

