## 11. STATISTICAL METHODS

### 11.1 Hypothesis

- |                            |                                                                                                                                                                                                                      |
|----------------------------|----------------------------------------------------------------------------------------------------------------------------------------------------------------------------------------------------------------------|
| 1° Null Hypothesis:        | Functional status and self-reported pain will reduce significantly in both groups, CG and EG, but no group interaction is expected.                                                                                  |
| 1° Alternative Hypothesis: | EG will show significantly more improvement in all primary and secondary outcomes as compared to CG.                                                                                                                 |
| 2° Null Hypothesis:        | Compared to healthy controls, patients with CNLBP will show no difference in postural control with optimal joint configuration variability when adjusting COM after destabilisation as compared to healthy controls. |
| 2° Alternative Hypothesis: | Patients with CNLBP will show different postural variability to adjust to destabilisation as compared to healthy controls.                                                                                           |
| 3° Null Hypothesis:        | Compared to healthy controls, patients with CNLBP will show no difference in cervical proprioception acuity as compared to healthy controls.                                                                         |
| 3° Alternative Hypothesis: | Patients with CNLBP will show reduced cervical proprioception acuity as compared to healthy controls.                                                                                                                |

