## **11.4 Planned Analyses**

Baseline imbalance between groups will be tested with a student t-test. Differences in means between healthy participants and patients with CNLBP will be analysed with independent student t-tests. A mixed (2) Group x (2) ME ANOVA with repeated measures during ME will be conducted for each dependent variable individually (Pain VAS, Functional Status ODI, Postural Control COM and CM, Proprioception JRE, and Motor Equivalence UCM).

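### The 2 x 2 ANOVA leaves the promised four-week follow-up test without an assigned analysis, and it is a valid but usually less precise use of the baseline already collected

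*Protocol*

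**What the plan says.** - **Planned comparison (Protocol 11.4):** "A mixed (2) Group x (2) ME ANOVA with repeated measures during ME will be conducted for each dependent variable individually". Pain (VAS) and function (ODI) are among the listed variables. The two measurement events are not named.
- **Effect of interest (11.1):** the first null hypothesis allows improvement in both arms, "but no group interaction is expected". The treatment question is therefore the group-by-time interaction.
- **Events in the randomised part (6.1):** sensorimotor training "in comparison to added LIT will be evaluated on three additional measurement events". These are T0, T1 and T2.
- **Timing of the primary endpoints (6.1):** "The primary endpoints are pain and function before" treatment (T0) and after the nine sessions.
- **Follow-up (6.1):** "Long-term effects will be tested four weeks after the last training session", that is, at T2.
- **Data available (9.2.1):** "The questionnaires will be filled in by the patients at every measurement event", namely BL, T0, T1 and T2. Two of the four precede treatment.
- **Use of baseline (11.4):** "Baseline imbalance between groups will be tested with a student t-test". No consequence is attached to the result, and no covariate adjustment is mentioned.
- **Synopsis:** "Repeated measure ANOVA with post-hoc analysis will be applied to test therapy effects". The number of time levels is not given.
- **Other analyses:** 11.4.2 says who carries out the primary analysis but names no test. 11.4.3 plans no secondary analysis. Sections 8.5 and 11.5 prescribe last observation carried forward.

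**The concern.** A time factor with two levels cannot hold T0, T1 and T2 together. If it holds T0 and T1, as the definition of the primary endpoints suggests, the follow-up comparison that 6.1 announces has no analysis. Because 11.4 does not name the events, and there are two pre-treatment and two post-treatment values, the pair could also be chosen after the data are seen.

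The second issue is efficiency. The only treatment comparison in the plan uses baseline as one level of the time factor, which amounts to subtracting it. In a trial of 20 to 30 patients, regressing on baseline would usually give a narrower interval from the same data. The protocol claims 80% power at 10 per arm, so precision matters even though it calls the trial a pilot and explorative.

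**Working it through.** **1. Where T2 could be analysed.** Section 6.1 promises a T2 test. Section 11.4 gives a two-level ANOVA with unnamed events. Section 11.4.2 names no test, and 11.4.3 plans nothing further. The synopsis does not state the number of levels. No section assigns T2 an analysis.

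**2. The plan's own figure.** Section 11.2 gives 10 per arm at alpha 5% and power 80%, based on two cited trials. Their effect and SD are not printed, so the figure can be neither reproduced nor refuted. The one printed between-group pair (1.4 and 0.19, from a gait study) gives d = 1.4/0.19 = 7.37 and 1 patient per arm by the normal formula, so it is not the source. At 80% power, 10 per arm implies d of about 1.32 (two-sided t-test). Nothing below depends on these figures.

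**3. What the 2 x 2 interaction is.** With two groups and two events, the interaction F equals the squared t statistic of a two-sample t-test on the change. On one simulated data set both were 0.427.

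**4. Precision.** Take equal variance s² at T0 and T1, correlation rho and n per arm. In units of 2s²/n, the variance of the estimated treatment effect is:
- change score: 2(1 − rho)
- baseline-adjusted: (1 − rho²), multiplied in small samples by 1 + 1/(2n − 4), which is 1 + 1/16 at n = 10

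The ratio is (1 + rho)/2 in large samples and (1 + rho)/2 × 17/16 at n = 10. The protocol gives no T0-T1 correlation, so rho is an assumption and is varied. The 0.937 in 9.2.1 is the test-retest reliability of the VAS, not a correlation across a five-week treatment period.

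| rho (assumed) | Large-sample ratio | Ratio at n = 10 | Change in variance at n = 10 | 10 per arm is worth (10/ratio) |
|---|---|---|---|---|
| 0.3 | 0.65 | 0.691 | −31% | 14.5 |
| 0.5 | 0.75 | 0.797 | −20% | 12.5 |
| 0.7 | 0.85 | 0.903 | −10% | 11.1 |
| 0.8 | 0.90 | 0.956 | −4% | 10.5 |
| 0.9 | 0.95 | 1.009 | +1% | 9.9 |

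Break-even at n = 10: rho = 2/(17/16) − 1 = 0.88. At n = 15 the penalty is 1 + 1/26 and break-even is 0.93.

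**5. Power and validity.** In 40,000 simulated trials per setting at 10 per arm, the effect was set so that the change-score test has 80% power. The adjusted test then had about 92%, 88%, 84%, 81% and 80% at rho 0.3, 0.5, 0.7, 0.8 and 0.9. Type I error was about 5% for both methods.

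**6. The imbalance test.** With 10 per arm and 18 degrees of freedom, an observed difference reaches two-sided p < 0.05 from 2.101 × √(2/10) = 0.94 SD. A true difference of 1.0 SD is detected 56% of the time, and 80% power needs about 1.32 SD.

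**The case against.** Several parts of the case for the plan stand.

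- **The layout suits the primary contrast.** Section 6.1 defines the primary endpoints at T0 and after treatment, and a 2 x 2 design fits that.
- **T2 is not shut out.** A reader might infer that the ANOVA cannot use the follow-up visit. Since 11.4 does not name the events, a second 2 x 2 on T0 and T2 would fit its wording. The defect is that no such analysis is stated.
- **The synopsis is not shown to contradict 11.4.** A reader might infer that post-hoc analysis has no object with two time levels. Simple effects, such as change within each arm, are an ordinary follow-up to a 2 x 2 interaction.
- **The interaction test is valid.** A reader might infer that chance baseline imbalance biases the result. Under randomisation it adds noise, which the standard error reflects. The issue is efficiency.
- **The imbalance test is not blind below 1.3 SD.** That figure is where power reaches 80%; smaller differences can be significant.
- **The gain depends on an unknown correlation** and disappears above about 0.88. Adjustment does not rescue the power either. For a true difference of 13 mm, the VAS threshold in 9.2.1, with an assumed SD of 20 mm and 10 per arm, simulated power rises only from about 21% to 29% (rho 0.3), 28% to 34% (0.5) and 43% to 47% (0.7).

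These points limit the criticism. They do not supply the missing T2 analysis or give a reason to prefer the change score.

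**Conclusion.** The point holds in two parts of different weight. The firmer part needs no assumption: 6.1 promises a T2 test, 11.4 names neither its events nor a T2 analysis, and 11.4.3 plans none. The second part is a recommendation on efficiency. At 10 per arm, baseline adjustment lowers the variance by about 31%, 20% or 10% at assumed T0-T1 correlations of 0.3, 0.5 or 0.7, with equal variances at the two events. At 0.8 little is gained, and above about 0.88 nothing. The figures are for T0 as covariate; using the mean of BL and T0 was not quantified. The t-test of baseline imbalance adds nothing, because any imbalance after randomisation is due to chance and the plan attaches no action to the result.

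**What to change.** In 11.4 and the synopsis, replace the 2 x 2 ANOVA for the randomised comparison by one baseline-adjusted model per outcome:

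- **Responses:** T1 and T2.
- **Fixed effects:** group, visit, group-by-visit, and the pre-treatment value (T0, or the mean of BL and T0; state which) by visit.
- **Inference:** small-sample degrees of freedom, for example Kenward-Roger.
- **Contrasts:** the adjusted experimental-minus-control difference at T1 with 95% CI as the main contrast, and the difference at T2 as the follow-up contrast.
- **Missing data:** use observed data in this model and align 8.5 and 11.5. Otherwise, for a patient who misses T2, a carried-forward T1 value would enter the T2 contrast as if observed.
- **Baseline:** tabulate by arm and delete the t-test of imbalance.

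The cost is wording and about one degree of freedom (17 instead of 18 for the T1 comparison at 10 per arm), with a negligible loss of precision if the correlation exceeds about 0.88. No further visits, data or patients are needed.

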### **11.4.1 Datasets to be analysed, analysis populations**

All participants will be analysed, intention-to-treat analysis will be applied. No sub-group analysis is intended.

### **11.4.2 Primary Analysis**

Primary analysis will be done by the PL at conclusion of all assessments. The PL will remain uninformed about group allocation until completion of analysis.

### **11.4.3 Secondary Analyses**

No secondary analysis is planned.

### **11.4.4 Interim analyses**

No interim analysis is planned.

### **11.4.5 Safety analysis**

Safety parameters will be monitored by the sponsor-investigator and the PL. At the end of the trial the quantities and natures of any adverse events will be summarised for the report.

### **11.4.6 Deviation(s) from the original statistical plan**

No deviations are intended.

## **11.5 Handling of missing data and drop-outs**

Missing data will be treated with last observation carried forward.

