## **8.5 Data Collection and Follow-up for withdrawn participants**

Withdrawn patients will be invited to take part at the assessments only. If refused, intention-to-treat analysis will be applied with carry-forward data.

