**9.2.5 Assessments in participants who prematurely stop the study**

Not applicable.

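### Filling missing visits by last observation carried forward can bias the VAS and ODI comparison, and Protocol 9.2.5 contradicts 8.5 on whether withdrawn patients are assessed

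*Protocol*

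**What the plan says.** Protocol 11.5 consists of one sentence: "Missing data will be treated with last observation carried forward". It makes no exception by outcome, visit or reason, and names no other method. Section 8.5 first offers follow-up, "Withdrawn patients will be invited to take part at the assessments only", and then says "If refused, intention-to-treat analysis will be applied with carry-forward data". Section 9.2.5, headed "Assessments in participants who prematurely stop the study", contains only a statement that it does not apply.

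The filled values enter the analysis described in 11.4: "A mixed (2) Group x (2) ME ANOVA with repeated measures during ME will be conducted for each dependent variable individually". VAS pain and ODI are among those variables. Section 11.4.1 sets the population: "All participants will be analysed, intention-to-treat analysis will be applied". Section 6.1 adds that "as-per-case analysis will also be conducted", without defining that term.

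Two other places bear on the choice of method. The first null hypothesis in 11.1 reads "Functional status and self-reported pain will reduce significantly in both groups, CG and EG, but no group interaction is expected", so improvement is expected in both arms even if the experimental training adds nothing. Section 7.4 gives an unexpected rise in pain as an example of why an intervention session or measurement is ended, and also lists a sustained increase of symptoms.

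**The concern.** Carry-forward assumes that an outcome stays where it was last seen. The protocol expects the opposite for both primary outcomes. A patient who leaves between T0 and T1 is given a change of exactly zero, and one who leaves between T1 and T2 is assumed stable for four weeks. The ANOVA then treats these values as measurements.

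Stopping may also depend on the primary outcome, because rising pain is among the reasons in 7.4. For such a patient, carry-forward keeps the earlier, better value and hides the worsening. Unequal drop-out is plausible, since the arms do different exercises and 6.1 accepts that patients cannot be blinded.

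With 10 patients per arm (11.2), each drop-out is 10% of an arm. At stake is whether the VAS and ODI contrast reflects the treatment or the pattern of who left. The conflict between 8.5 and 9.2.5 adds to this: staff who follow 9.2.5 would not collect T1 and T2 values that 8.5 makes available, and carry-forward would fill the gap.

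**Working it through.** **Inputs from the protocol.** 10 patients per arm (11.2); relevant difference 13 mm on the VAS and 4 points on the ODI (9.2.1); improvement expected in both arms (11.1). The protocol has no figure for the effect of missing data that could be reproduced.

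**Assumed inputs.** Drop-out 0% to 30% per arm. Improvement in both arms of 13 to 26 mm (VAS) or 4 to 8 points (ODI), that is, one to two times the relevant difference. For the simulations: 20 mm improvement, SD 20 mm at each visit, correlation 0.5, drop-out completely at random.

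**Formula.** Let I be the mean improvement and d the drop-out share, with E and C for the experimental and control arms. If drop-out is unrelated to the individual's change and T0 is carried to T1:

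apparent difference = I_E(1 − d_E) − I_C(1 − d_C)

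Only when I_E = I_C = I does this reduce to I(d_C − d_E).

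**No true difference, VAS**
- Equal drop-out: I × 0 = 0 mm.
- E 10%, C 30%: 13 × 0.2 = 2.6 mm to 26 × 0.2 = 5.2 mm, falsely favouring the experimental arm.
- E 30%, C 10%: the same amounts against it.

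**No true difference, ODI**, 10% versus 30%: 4 × 0.2 = 0.8 to 8 × 0.2 = 1.6 points.

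**True difference of 13 mm**
- 10% in each arm: 13 × 0.9 = 11.7 mm.
- 20% in each arm: 13 × 0.8 = 10.4 mm.
- E 30%, C 10%, control improvement 13 mm: 26 × 0.7 − 13 × 0.9 = 6.5 mm.
- E 30%, C 10%, control improvement 26 mm: 39 × 0.7 − 26 × 0.9 = 3.9 mm.

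A true 4-point ODI difference with 20% drop-out in each arm becomes 4 × 0.8 = 3.2 points.

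**Simulation.** 6,000 trials per scenario, 10 per arm, two-sided 5% t-test on change from T0 to T1, which is equivalent to the group-by-time interaction in a 2x2 ANOVA. Drop-out is random at the stated rate.

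| True effect | Drop-out E / C | Mean difference, LOCF | Rejections, LOCF | Rejections, observed data only |
|---|---|---|---|---|
| 0 mm | 20% / 20% | about 0 mm | 4.9% | 5.0% |
| 0 mm | 10% / 30% | 4.1 mm | 7.7% | 5.3% |
| 0 mm | 0% / 30% | 5.9 mm | 11.0% | 5.1% |
| 13 mm | 20% / 20% | 10.3 mm | 18.2% | 22.6% |

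With a true 13 mm effect and no missing data the rejection rate was 27.2%. The fall from about 27% to about 23% is due to lost patients; the further fall to about 18% is due to carry-forward.

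**Scale.** The SD of change is 20 × √(2 × (1 − 0.5)) = 20 mm, so the standard error of the difference with complete data is 20 × √(2/10) = 8.9 mm. With exactly one, two or three drop-outs in one arm and none in the other, and 20 mm improvement, the shift is 2, 4 or 6 mm. The false-positive rate is then about 5%, 6% and 10%.

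**8.5 against 9.2.5.** Section 8.5 invites withdrawn patients to the assessments and uses carry-forward only after refusal. Section 9.2.5, under a heading covering the same situation, says nothing applies. No text ranks one above the other.

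**The case against.** - **Not every missing value is carried forward.** A reader might infer this from 11.5. But 9.2.1 prorates the ODI when sections are unanswered, and 8.5 makes carry-forward the fallback after an attempt at follow-up. This stands: the point concerns missing visits.
- **9.2.5 does not cancel the visits in 8.5.** A reader might infer that it does. Its entry matches neighbouring headings that are also marked as not applicable, and it could mean only that no extra assessments are defined for those who stop. Nothing gives it precedence over the explicit invitation in 8.5. This stands: it is a contradiction to resolve, not a withdrawal of the offer.
- **Bias is not inevitable.** With no true effect, equal drop-out and equal improvement it is zero. The simple product of drop-out difference and improvement holds only if both arms improve equally.
- **The sizes rest on assumptions.** One or two drop-outs shift the estimate by 2 to 4 mm against a standard error of 8.9 mm, and the false-positive rate barely moves. The larger figures need a marked imbalance. Attributing the whole power fall from 27% to 18% to carry-forward would also be wrong, since about half is lost data.
- **The trial is an explorative pilot with a short primary interval, and a further analysis is planned.** This lowers the severity but does not remove the point. The trial still tests a between-arm hypothesis on VAS and ODI, and the as-per-case analysis is undefined, so it cannot be relied on as a missing-data sensitivity analysis.
- **The detail could wait for an SAP.** It could if the protocol were silent, but 11.5 fixes a method.

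**Conclusion.** The point holds in a limited form. Carry-forward is the only method stated for missing visits, and it conflicts with the protocol's own expectation of improvement in both arms and with the link in 7.4 between stopping and pain. It can bias the VAS and ODI comparison in either direction if drop-out differs between arms, and it shrinks a true effect if drop-out is equal.

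The size cannot be fixed from the document. Under the stated assumptions a 20-percentage-point imbalance produces a false 2.6 to 5.2 mm, which is 20% to 40% of the 13 mm threshold (2.6/13 and 5.2/13). Equal 20% drop-out takes a true 13 mm to 10.4 mm and costs about 5 points of power beyond the loss of the patients themselves. These figures assume drop-out unrelated to the individual's change. Withdrawal because of pain would alter them, and observed-data analyses would then not be safe either.

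The conflict between 8.5 and 9.2.5 is real but separate, and does not by itself cause the bias. Severity: should-fix.

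**What to change.** 1. In 11.5 and 8.5, replace carry-forward by a likelihood-based mixed model on all observed values of all randomised patients, with T0 as covariate or as part of the outcome vector. State that it relies on data missing at random.
2. In 11.4, replace the 2x2 ANOVA by the same model for the treatment comparison, so that 11.4 and 11.5 agree.
3. Keep carry-forward at most as a labelled sensitivity analysis. Add a sensitivity analysis for patients who withdraw because of pain, since missing at random is least credible for them.
4. Reconcile 9.2.5 with 8.5 so that the T1 and T2 assessments already offered to withdrawn patients are collected.

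The cost is protocol wording in 8.5, 9.2.5, 11.4 and 11.5, settled before outcome data are seen, and a modest amount of extra analysis. No visits are needed beyond those that 8.5 already offers.
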